**Outcomes:**

Primary end point will be composite of mortality (30d); ICU stay more than 5daysand post-operative arrhythmia requiring intervention (48h). Secondary end point length of hospital stays(days), length of mechanical ventilation (days), myocardial biomarkers (troponin, CKMB), ventricular function by echo, CMO, inotropic score sample size calculated with an online calculator basis of an error of 0.05 and a B error of 0.2 to detect an absolute difference of 15% in composite end point between the two gps yielded 137 in each arm, the results will be presented as mean (SD), median (interquartile (range), or proportion. Using relative risk for statistical analysis and log rank. A P value of less than 0.05 will be considered statistically significant. Statistical analyses will be carried out using the SPSS

**Safety monitoring and interim results:**

Both cardioplegia solutions are already in use and FDA approved there is no safety concerns at the time being. However, an interim analysis will be carried on every 6months and the principal investigator will decide whether to stop or carry on if any major discrepancies in outcomes are observed

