Also, an animal study by Chen Y et al, on piglets that were randomized to either a single dose of HTK or multidose cold blood cardioplegia. No significant differences were noted in the myocardial lactate content, ATP content, and histopathological score between both groups.

Finally, a retrospective report by E Qulisy et al concluded that Custodiol cardioplegia is associated with less myocardial protection and higher adverse outcomes compared to blood cardioplegia in pediatric age group undergoing cardiac surgery.

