**Blinding:**

Surgeons will know the type of cardioplegia in the OR while another assessor will be blinded.

Sample size calculated with an online calculator based on α _error of 0.05 and β _error of0.2 to detect an absolute risk difference of 15% in composite end point between the twogroups yielded 137 in each arm, the results will be presented as mean (SD), median

(interquartile range), or proportion. Using relative risk and log rank for statistical analysis. A P value of less than 0.05 will be considered statistically significant. Statistical analyses will be carried out using the SPSS.

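### Six-monthly interim comparisons, their number not given, with stopping at the principal investigator's judgement and one unadjusted P<0.05, leave the false-positive rate uncontrolled

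*Protocol*

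**What the plan says.** The section on safety monitoring and interim results gives the whole monitoring plan: "an interim analysis will be carried on every 6months and the principal investigator will decide whether to stop or carry on" if between-group differences in outcome are seen that count as major. It does not say how large a difference is major, in which outcome or in which direction. It also does not say how many looks there will be, or what conclusion may be drawn if the trial stops early. It introduces the plan by noting that both solutions are in use and approved, and that "there is no safety concerns at the time being".

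The analysis paragraph appears under Blinding and again under Outcomes. It sets one criterion: "A P value of less than 0.05 will be considered statistically significant". The sample size uses an alpha of 0.05 and a "β _error of0.2", is meant "to detect an absolute risk difference of 15% in composite end point between the twogroups", and "yielded 137 in each arm". Neither version mentions interim looks.

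The hypothesis in the Detailed Description is non-inferiority of Custodiol. Among the reports in the literature review is a retrospective one concluding that "Custodiol cardioplegia is associated with less myocardial protection and higher adverse outcomes compared to blood cardioplegia".

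**The concern.** A 5% error rate belongs to one test. If the accumulating data are compared every six months and the trial can end because a difference looks large, chance has several opportunities to produce that difference. The final P value then no longer means what the protocol says it means. A later analysis cannot repair this, because the stopping rule was never fixed and its error rate cannot be reconstructed.

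Two further things are at stake. A trial that stops because the observed difference is large will, on average, report too large a difference. And judging a between-group discrepancy requires someone to look at results by arm during enrolment. Surgeons already know the allocation, and two parts of the composite (ICU stay beyond 5 days, arrhythmia needing intervention) involve clinical judgement.

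A boundary could reasonably be left to a SAP, which is not shown, so its absence alone is not the point. The point is what the protocol does fix: recurring looks, an undefined trigger, one person's discretion and one unadjusted threshold. A boundary in a SAP would still conflict with that text.

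**Working it through.** **Inputs from the Protocol.** Alpha 0.05, power 80%, absolute difference 15 percentage points, 137 per arm (274 in total), a look every 6 months.

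**Assumptions, because the Protocol is silent.** Two-sided testing; equally spaced looks; 2 to 10 looks including the final one; a control rate where one is needed.

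**1. Does 137 allow for interim looks?** No control rate is stated, so 137 cannot be derived from the stated inputs alone. At 20% versus 35%, with mean rate 0.275:

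- Pooled: n = [1.96√(2×0.275×0.725) + 0.8416√(0.35×0.65 + 0.20×0.80)]² / 0.15² = 137.9, so 138.
- Unpooled: n = (1.96 + 0.8416)² × (0.2275 + 0.16) / 0.0225 = 135.2, so 136.

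The stated 137 lies between the two. It fits an ordinary single-analysis calculation. Other control rates and a one-sided test can also give 137, so this shows consistency and does not identify the calculation used.

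**2. False-positive rate if P<0.05 could end the trial at every look.** With no true difference, the statistic at look k of K is Z_k = (X_1 + … + X_k)/√k, with X_i independent N(0,1). The overall error is 1 − P(|Z_k| ≤ 1.96 for all k), found by numerical integration. The third column uses 2.576 (P<0.01) at the interims and 1.96 at the end. The fourth uses 3.291 (P<0.001) at the interims and 1.96 at the end.

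| Looks in total | P<0.05 at every look | P<0.01 at interims, 0.05 at end | P<0.001 at interims, 0.05 at end |
|---|---|---|---|
| 1 | 5.0% | 5.0% | 5.0% |
| 2 | 8.3% | 5.5% | 5.0% |
| 3 | 10.7% | 5.9% | 5.1% |
| 4 | 12.6% | 6.2% | 5.1% |
| 6 | 15.5% | 6.8% | 5.1% |
| 8 | 17.6% | 7.2% | 5.2% |
| 10 | 19.3% | 7.6% | 5.2% |

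A simulation with a binary endpoint, 137 per arm and a common event rate of 30% agrees with the second column: 8.5%, 10.7%, 12.9% and 15.4% for 2, 3, 4 and 6 looks.

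**3. The non-inferiority reading.** If an early stop could itself declare non-inferiority at one-sided 0.025, simulation gives an error of about 4.2% with 2 looks, 5.4% with 3, 7.8% with 6 and 9.7% with 10. The ratio to the nominal level is nearly the same as in the second column.

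**4. Exaggeration after an early stop.** At a mean event rate of 27.5%, P<0.05 needs an observed difference of at least 1.96√(0.275×0.725×2/n). That is 21.2 points at n = 34 per arm (about a quarter of the trial), 14.9 points at n = 69 (half) and 10.6 points at n = 137. A stop at the first of these could only report a difference well above the 15 points that the trial was sized for.

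**5. Power with P<0.001 at interims and 0.05 at the end.** At 20% versus 35% with 137 per arm, power is 80.0% against 79.9% for a single analysis. The difference is within simulation error.

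**The case against.** The strongest objection is that no inflation figure follows from the text. The 0.05 criterion stands in the analysis paragraphs, and the monitoring section names no P value. If the investigator regarded only very strong differences as major, the last two columns of the table would apply and the harm would be small. This stands: the error rate is unknown, not shown to be high. It does not rescue the plan, because an undefined trigger may be looser than P<0.05 as well as stricter.

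Second, the section is about safety and the hypothesis is non-inferiority. If looks could stop the trial only for harm with Custodiol, the chance of a false conclusion in its favour could not exceed the final test's 2.5% one-sided, since stopping for harm only removes opportunities to claim success. This is correct. But the text limits neither the direction of the discrepancy nor what may be concluded after a stop.

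Third, a symmetric P<0.001 rule is a poor harm rule. At 69 per arm with 1 death in one arm, a z test crosses it only at 13 deaths in the other: z = (12/69)/√(0.1014×0.8986×2/69) = 3.38, whereas 12 deaths give 3.21. This stands, and it is why the boundary below governs claims only.

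A reader might also infer several stronger things that the documents do not support:

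- **The false-positive rate is two to three times 5%.** That needs about 3 to 6 looks and P<0.05 as the trigger. The Protocol gives neither.
- **The looks are unlimited.** Their number is unspecified, but 274 patients bound it.
- **The principal investigator is unblinded.** Only surgeons are said to know the allocation. Judging discrepancies implies seeing results by arm, but that is an inference.
- **The safety statement is refuted by the Protocol's own review.** The two adverse reports are retrospective. The review also cites a randomised trial favouring the Custodiol-type solution and a piglet study with no significant differences against blood cardioplegia. The statement needs reconciling with that mixed evidence; it is not shown to be false.

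**Conclusion.** The point holds as a lack of control, not as a known multiple of 5%. The Protocol fixes recurring comparative looks and discretionary stopping on an undefined criterion, and pairs them with one unadjusted threshold. The stated 5% therefore is not assured. The range of about 8% to 19% for 2 to 10 looks depends on three assumptions: P<0.05 at each look, equal spacing, and freedom to claim a result after an early stop. With stricter triggers the inflation would be slight, and with stopping for harm alone there would be none in Custodiol's favour. It should be fixed before the first interim comparison, because a discretionary stop on a chance difference cannot be corrected afterwards.

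**What to change.** Amend the section on safety monitoring and interim results as follows.

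1. State that an early stop may support a claim on the composite, whether of a difference or of non-inferiority, only if P<0.001 at that interim look, with the final test at 0.05. State whether these levels are two-sided.
2. Keep stopping for safety separate from this boundary, and say that a safety stop does not by itself support a claim of efficacy or non-inferiority.
3. Have the comparison run by the trial's analyst, not by the blinded assessor (which would risk unblinding the only role described as blinded) or by treating surgeons. Release results by arm to the principal investigator only if the boundary or a safety concern is reached.
4. Reconcile the statement that "there is no safety concerns at the time being" with the conflicting reports in the literature review.

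The cost is one paragraph of amendment and no extra patients. Power is essentially unchanged, checked only at the assumed 20% versus 35%. The downside is that a moderate early difference can no longer end the trial with a positive claim.
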